#### Sample size

Based on the study-related literature, experts’ opinions, and previous study results [28, 30, 31, 37–39], the following will be assumed: the average post-treatment changes in the 24-hour proteinuria level in the SYKFT group, losartan potassium 50 mg group, losartan potassium 100 mg group, SYKFT + losartan potassium 50 mg group, and SYKFT + losartan potassium 100 mg group will be 1.00, 1.00, 1.05, 1.08, and 1.10 g per 24 hours, respectively. The standard deviation will be 0.2 g in every group, the significance level will be α = 0.05, and the power will be (1-β) = 0.9. Adjusting for 20% loss, we will need a sample size of 144 participants in each group. Thus, the total number of participants will be 720.

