#### Statistical analysis

The principal analysis will be performed according to the intent-to-treat principle in a full analysis set comprising participants who have been randomly allocated into groups and have taken at least one dose of the study drugs. The set will be obtained after the minimal and reasonable removing method has been used among all randomized participants. Missing data will be adjusted using the last observation carried forward method. Patients who complete the study and comply well with the study protocol without major protocol violations will constitute the per-protocol set, and good compliance will be defined as the fact that the dose of the drug actually taken equals 80% to 120% of the required dose. All participants who have taken at least one dose of the study drugs will be included in the safety analysis set. The full analysis set will be used as the primary analysis population for efficacy analysis, while the per-protocol set will be used as the secondary analysis population for efficacy analysis. The safety analysis set will be used for safety analysis. Detailed classification criteria for the data sets will be determined and be kept on record by a data verification meeting before the database is locked.

Frequency tables, percentages, or constituent ratios will be used to describe the categorical data. Mean and standard deviation or median, first quartile, and third quartile will be used to describe continuous data. Categorical data will be analyzed by the chi-squared test, Fisher’s exact test, the Wilcoxon rank sum test, and the CMHX2 test. Continuous data in each group will be described by mean ± standard deviation and will undergo analysis of variance followed by pairwise comparison. The Wilcoxon rank sum test or Wilcoxon signed rank test will be used if the data exhibit an abnormal distribution. Covariance analysis will be used to assess factors that may affect the efficacy outcomes when appropriate. All statistical analyses will be run using SAS 9.1.3 software (version 9.1.3; SAS Institute, Inc., Cary, NC, USA). Hypothesis testing will uniformly involve a two-tailed test, and both the test statistic quantity and corresponding *P* value will be calculated. Statistical significance will be declared if the *P* value is <0.05.

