## Discussion

Primary glomerulonephritis is a major cause of CKD [40–42]. Effective control of proteinuria and protection of kidney function play key roles for the treatment of CKD. Previous research has demonstrated that SYKFT provides a greater advantage in improving the clinical symptoms of CKD, controlling proteinuria, protecting kidney function, and reducing the side effects of Western medicine [38, 39]. SYKFT includes Chinese medicinal herbs with synergic effects, demonstrate stable long-term efficacy, have no toxicity or side effects after many years of use, and exhibit good treatment compliance among patients. However, there is a lack of data derived from randomized controlled trials on the use of SYKFT. We have designed the present multicenter, prospective, double-blind, double-dummy, randomized controlled clinical trial among various sites distributed in 19 provinces and municipalities. An important feature of this study is that participants have a wide geographical distribution and many participating sites are included; thus, poor generalization resulting from a narrow geographical distribution and single center can be avoided, allowing for relatively good generalization and applicability.

The results of this trial will provide solid evidence for evaluation of the efficacy and safety of SYKFT versus losartan potassium in controlling proteinuria in patients with primary glomerulonephritis. Moreover, we hypothesize that SYKFT + losartan potassium therapy can decrease the level of proteinuria in patients with primary glomerulonephritis to a larger extent than SYKFT or losartan potassium therapy alone.

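### The single stated power of 0.9 is tied to no comparison, and on the plan's own figures the losartan 100 mg contrasts have only 47% to 56% power

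*Protocol article*

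**What the plan says.** The Sample size section lists five assumed mean changes in 24-hour proteinuria, in the order SYKFT, losartan 50 mg, losartan 100 mg, SYKFT + losartan 50 mg, SYKFT + losartan 100 mg. They "will be 1.00, 1.00, 1.05, 1.08, and 1.10 g per 24 hours, respectively". It adds "The standard deviation will be 0.2 g in every group", then "the significance level will be α = 0.05, and the power will be (1-β) = 0.9". It concludes "Adjusting for 20% loss, we will need a sample size of 144 participants in each group" and "Thus, the total number of participants will be 720". The section does not say which comparison the 0.9 belongs to.

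The questions are set elsewhere in the article. The Background section gives the aim as comparing SYKFT with losartan. The Discussion hypothesises that the combination lowers proteinuria "to a larger extent than SYKFT or losartan potassium therapy alone". The Statistical analysis section plans analysis of variance followed by pairwise comparison, with significance at P < 0.05, and says "Hypothesis testing will uniformly involve a two-tailed test". Its primary population is the full analysis set, with missing values filled by last observation carried forward.

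**The concern.** Every stated question compares two arms, or a combination with its components, but the sample size section offers one power figure for five means. Those means imply differences of 0, 0.05, 0.08 and 0.10 g for the comparisons of interest. With a common SD and equal arms, one sample size cannot give all of them the same power.

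The interpretation of a negative result is at stake. If the assumed 0.05 g benefit of adding SYKFT to losartan 100 mg is real, the planned test would miss it about half the time. A reader who takes 0.9 to cover that test could read the miss as showing no added benefit. Similarly, a non-significant difference between SYKFT and losartan 100 mg could be taken as showing that the two are equivalent, although the plan itself assumes that SYKFT does 0.05 g less well.

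**Working it through.** **Inputs** (Sample size and Statistical analysis sections): means 1.00, 1.00, 1.05, 1.08 and 1.10 g; SD 0.2 g; two-sided alpha 0.05; target power 0.9; 20% loss; 144 randomised per arm. Evaluable per arm: 144 × 0.8 = 115.2, taken as 115. If carrying observations forward keeps every patient in the analysis, it is 144.

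**1. Trying the stated figure with the five-group F test.** The mean of the five means is 5.23/5 = 1.046. The squared deviations sum to 2 × 0.002116 + 0.000016 + 0.001156 + 0.002916 = 0.00832. The noncentrality is n × 0.00832/0.04, which at n = 115 is 23.9 and gives 98.5% power. For 90% the test needs 76 evaluable per arm, and 76/0.8 = 95 randomised. This is not 144.

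**2. Trying it with single pairwise tests.** n = 2 × SD² × (1.960 + 1.282)² / d² = 0.841/d², rounded up.

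| Difference d | Evaluable per arm for 90% | Randomised per arm (÷ 0.8) |
|---|---|---|
| 0.10 g | 85 | 107 |
| 0.08 g | 132 | 165 |
| 0.05 g | 337 | 422 |

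None gives 144. The t distribution adds one patient per arm to the evaluable numbers (86, 133, 338).

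**3. Power of each contrast that answers a stated question.** Power ≈ Φ(d/SE − 1.960), with SE = 0.2 × √(2/n). At n = 115, SE = 0.02637; at n = 144, SE = 0.02357.

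| Contrast | d | Power at 115 | Power at 144 |
|---|---|---|---|
| SYKFT + losartan 100 vs losartan 100 | 0.05 g | Φ(1.896 − 1.960) = 47% | Φ(2.121 − 1.960) = 56% |
| SYKFT vs losartan 100 | 0.05 g, SYKFT lower | 47% | 56% |
| SYKFT + losartan 50 vs losartan 50 | 0.08 g | Φ(3.033 − 1.960) = 86% | Φ(3.394 − 1.960) = 92% |
| SYKFT + losartan 50 vs SYKFT | 0.08 g | 86% | 92% |
| SYKFT + losartan 100 vs SYKFT | 0.10 g | Φ(3.792 − 1.960) = 97% | Φ(4.243 − 1.960) = 99% |
| SYKFT vs losartan 50 | 0 | 5% (alpha only) | 5% (alpha only) |

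The noncentral t distribution gives the same whole percentages. If the loss was instead applied as n × 1.2, so that 120 per arm are evaluable, the 0.05 g contrasts have 49%.

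**4. The add-on effect pooled over dose.** The average difference is (0.08 + 0.05)/2 = 0.065 g, with 230 against 230 patients at 115 per arm. SE = 0.2 × √(2/230) = 0.01865 and 0.065/0.01865 = 3.485. Power is about 93.5% by noncentral t, and 97% with 288 against 288, using the full alpha of 0.05.

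**The case against.** Three arguments on the other side carry weight.

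First, the shortfall is not general. A reader might infer from the 47% that the trial is underpowered for its questions as a whole. The figures do not support that. Of the four combination-versus-component contrasts, one exceeds 90% at either sample size, and two have 86% at 115 and 92% at 144. The omnibus test also exceeds 90%. The Discussion's hypothesis names no losartan dose, and the chance that at least one of the two add-on contrasts is significant at 115 per arm, without multiplicity adjustment, is about 1 − (1 − 0.858)(1 − 0.474) = 93%. That still says nothing about the losartan 100 mg contrast taken alone.

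Second, the section never claims 0.9 for every pair. It lists two identical means, so a careful reader would not assume that. This stands, but the figure is then attached to no comparison at all, and the reader cannot tell what it describes.

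Third, a reader might conclude that 144 is an arithmetic error. The documents do not show that. Some unstated routes do reach it: a three-arm analysis of variance of SYKFT, losartan 50 mg and their combination at alpha 0.05 needs 120, and 120 × 1.2 = 144; the 0.10 g difference at alpha 0.05/4 needs 115, and 115/0.8 = 144. Because several routes fit and none is stated, the origin of 144 cannot be settled from the article. Neither route raises the losartan 100 mg contrasts to 90%.

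Finally, the article condenses a full protocol that is not shown and may name the comparison. However, the means, SD, alpha and sample size are all printed, and they are enough to show where 0.9 does not apply. Nor should the contrasts be combined into a joint success probability, because no joint success rule is stated.

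**Conclusion.** The point holds for the losartan 100 mg comparisons. On the plan's own assumptions, one of the two add-on contrasts (SYKFT + losartan 100 mg against losartan 100 mg) and one of the two direct comparisons of SYKFT with losartan have 47% power at 115 per arm and 56% at 144, against a stated 0.9. The other direct comparison, with losartan 50 mg, has an assumed difference of zero, so a superiority test has no power beyond alpha. The losartan 50 mg add-on is close to target, and the combination with losartan 100 mg against SYKFT is above it.

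These figures assume that the stated means are reductions, that the SD is 0.2 g in every arm, and that each contrast is tested at two-sided 0.05 without adjustment. The upper figures also assume that all 144 per arm are analysed and that carrying observations forward leaves the means and SD unchanged. Any multiplicity adjustment would lower the power: at alpha 0.0125 the 0.05 g contrasts have 27% at 115 per arm.

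**What to change.** In the Sample size section, replace the single 0.9 with the power of each named contrast, as in the table above, at both 115 and 144 per arm. Name the comparison that 144 per group was sized for, the alpha used, and how the 20% loss was applied. In the Statistical analysis section, state that a non-significant contrast with losartan 100 mg will not be read as evidence of no added benefit or of equivalence.

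This costs some rewording and no patients. Its only downside is that it shows openly that the losartan 100 mg contrasts are underpowered.

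Optionally, before unblinding, prespecify as a supporting analysis the SYKFT add-on effect pooled over the two losartan doses and stratified by dose (0.065 g on the plan's means; 93.5% power at 115 per arm and 97% at 144, at the full alpha of 0.05). It averages over dose and does not address SYKFT against losartan. Making it the primary comparison would be a design change after recruitment had started, and the correction does not require it.

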#### Statistical analysis

The principal analysis will be performed according to the intent-to-treat principle in a full analysis set comprising participants who have been randomly allocated into groups and have taken at least one dose of the study drugs. The set will be obtained after the minimal and reasonable removing method has been used among all randomized participants. Missing data will be adjusted using the last observation carried forward method. Patients who complete the study and comply well with the study protocol without major protocol violations will constitute the per-protocol set, and good compliance will be defined as the fact that the dose of the drug actually taken equals 80% to 120% of the required dose. All participants who have taken at least one dose of the study drugs will be included in the safety analysis set. The full analysis set will be used as the primary analysis population for efficacy analysis, while the per-protocol set will be used as the secondary analysis population for efficacy analysis. The safety analysis set will be used for safety analysis. Detailed classification criteria for the data sets will be determined and be kept on record by a data verification meeting before the database is locked.

Frequency tables, percentages, or constituent ratios will be used to describe the categorical data. Mean and standard deviation or median, first quartile, and third quartile will be used to describe continuous data. Categorical data will be analyzed by the chi-squared test, Fisher’s exact test, the Wilcoxon rank sum test, and the CMHX2 test. Continuous data in each group will be described by mean ± standard deviation and will undergo analysis of variance followed by pairwise comparison. The Wilcoxon rank sum test or Wilcoxon signed rank test will be used if the data exhibit an abnormal distribution. Covariance analysis will be used to assess factors that may affect the efficacy outcomes when appropriate. All statistical analyses will be run using SAS 9.1.3 software (version 9.1.3; SAS Institute, Inc., Cary, NC, USA). Hypothesis testing will uniformly involve a two-tailed test, and both the test statistic quantity and corresponding *P* value will be calculated. Statistical significance will be declared if the *P* value is <0.05.

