#### Quality control and quality assurance

A Clinical Trial Standard Operating Procedures training conference was conducted in Beijing to ensure that each site conducts the study according to the Standard Operating Procedures. All investigators from each site attended the conference and received training.

The monitoring procedures will be conducted at every site by the contract research organization throughout the study. The investigator is responsible for providing all source documents, including the CRFs and other study-related files. Confidentiality agreements for each participant will be implemented according to local regulations. The investigator will periodically monitor the CRFs according to a monitoring plan to ensure completeness of the study and validity and accuracy of the data. After verifying the correctness of the research data and original records, these data will be simultaneously entered into the CRFs and input into an electronic data capture system. The electronic data capture system allows only users with specific authority to handle the data; thus, error can be avoided.

At each study site, blood and urine samples will be collected at weeks 0, 24, and 48. After being processed and frozen, the samples will be transported to the central laboratory for unified measurement to reduce data bias.

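### Last observation carried forward in the principal analysis costs power even with equal loss, and biases the small planned differences if loss is unequal

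*Protocol article*

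**What the plan says.** Under Statistical analysis, the Protocol article bases the principal efficacy result on a full analysis set of "participants who have been randomly allocated into groups and have taken at least one dose of the study drugs". One missing-data method is named: "Missing data will be adjusted using the last observation carried forward method". The per-protocol set is the secondary efficacy population.

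Under Sample size, the assumed mean changes in 24-hour proteinuria for SYKFT, losartan 50 mg, losartan 100 mg, SYKFT + losartan 50 mg and SYKFT + losartan 100 mg "will be 1.00, 1.00, 1.05, 1.08, and 1.10 g per 24 hours, respectively". On spread: "The standard deviation will be 0.2 g in every group". On loss: "Adjusting for 20% loss, we will need a sample size of 144 participants in each group".

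Outcome measures schedules the outcome at weeks 0, 4, 8, 12, 24, 36 and 48. Under Withdrawal, patients who meet the criteria leave the study and are not replaced. The Discussion hypothesizes that the combination lowers proteinuria more than either drug alone.

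**The concern.** LOCF is a method the document has chosen, not a detail left open. It assumes that proteinuria stays where it was at the last visit attended. Over 48 weeks of treatment that fails if the response is still building at dropout or reverses after the drug is stopped. It also enters a guessed final value as if it had been measured.

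This trial is sensitive to that error because of its own planning figures. Each arm is expected to change by about 1 g, while the hypothesized gains of combination over single drug are 0.05 to 0.10 g. The mean is thus 10 to 20 times the effect, and a small difference between arms in how much of that 1 g goes unrecorded is not small against the effect. Even without such a difference, early values mixed with final values widen the spread and use up the power that the loss allowance was meant to protect.

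**Working it through.** **Inputs from the Protocol article.** Mean changes 1.00, 1.00, 1.05, 1.08 and 1.10 g; SD 0.2 g; 144 per arm; 20% loss; two-sided 5% tests (Sample size, Statistical analysis). Losartan reaction rates: orthostatic hypotension below 1%, hyperkalaemia 1.5% (Adverse events).

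**Assumptions not in the document.** f, the share of the final change already reached at the last observed visit; d, the loss in each arm; final visit taken as week 48; carried values have the same within-group SD of 0.2 g.

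**The plan's own figures.** 20% of 144 = 28.8, so about 29 patients per arm would be imputed and 115 observed. A five-group analysis of variance on the stated inputs gives 76 per group, or 95 after dividing by 0.8, so it does not reproduce 144. That is a separate matter and nothing below rests on it; 144 is taken as given.

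**Formulas.** Expected arm mean under LOCF = mu × [1 − d(1 − f)]. Variance under LOCF = 0.2² + d(1 − d) × [mu(1 − f)]². Bias = LOCF difference minus planned difference.

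**1. Equal 20% loss, f = 0.5.**
- Every difference is multiplied by 1 − 0.20 × 0.5 = 0.90: 0.05 becomes 0.045, 0.08 becomes 0.072, 0.10 becomes 0.09 g.
- Variance at mu = 1.00: 0.04 + 0.16 × 0.25 = 0.08, SD 0.28 g. At mu = 1.08: 0.04 + 0.16 × 0.2916 = 0.0867, SD 0.29 g.
- Power for the 0.08 g contrast: standard error √[(0.08 + 0.0867)/144] = 0.034; 0.072/0.034 gives about 56%.
- For comparison, 115 completers per arm with SD 0.2 g give about 86%, and 144 fully observed per arm give 92%.
- Range over f: at f = 0.75, LOCF gives about 81%; at f = 0.9, about 90%, which is above the completers.

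**2. Unequal loss, gap bounded by the document's own rates.** If every listed hypotension and hyperkalaemia case withdrew, losartan arms would lose at most 1 + 1.5 = 2.5 points more than SYKFT alone. With f = 0.5 and mu about 1 g, bias = 0.025 × 0.5 × 1.0 = 0.0125 g.

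**3. Unequal loss, illustrative 10-point gap (25% in the arm with the larger change, 15% in the other).**

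| Planned difference (g) | Bias at f = 0.5 | Left at f = 0.5 | Bias at f = 0.75 | Bias at f = 0.9 |
|---|---|---|---|---|
| 0.05 (1.05 vs 1.00) | −0.056 | −0.006 | −0.028 | −0.011 |
| 0.05 (1.10 vs 1.05) | −0.059 | −0.009 | −0.029 | −0.012 |
| 0.08 (1.08 vs 1.00) | −0.060 | 0.020 | −0.030 | −0.012 |
| 0.10 (1.10 vs 1.00) | −0.063 | 0.038 | −0.031 | −0.013 |

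Example: 1.08 × (1 − 0.125) − 1.00 × (1 − 0.075) = 0.945 − 0.925 = 0.020 g. With SD held at 0.2 g, power at 144 per arm falls from 92% to about 13%.

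With the loss reversed (15% in the arm with the larger change), the same contrast becomes 1.08 × 0.925 − 1.00 × 0.875 = 0.124 g, a bias of +0.044 g. The error can therefore run either way. For SYKFT versus losartan 50 mg, planned as equal, the 10-point gap creates a difference of 0.10 × 0.5 × 1.0 = 0.05 g.

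**The case against.** The strongest reply is that the 20% is one allowance applied to every group, not a forecast and not a split by arm. With equal loss and a common course LOCF only shrinks the differences, which works against the superiority hypothesis rather than for it. That is right as to direction; the loss of power remains.

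A reader might infer that LOCF is likely to erase the whole planned effect. The document does not support that:
- For SYKFT + losartan 100 mg versus losartan 100 mg, both arms take the same losartan dose, so losartan reactions explain no gap. The article reports no obvious adverse reactions to SYKFT.
- For SYKFT versus losartan, the quoted rates reach 2.5 points at most. Rising blood pressure may be treated with permitted drugs, and neither it nor lack of effect is a listed withdrawal reason, although the wording on unsuitability to continue is broad.
- Erasing 0.10 g takes roughly a 10-point gap with baseline carried for every dropout, or 20 points with half the response reached. Since the outcome is measured from week 4, carrying baseline for all of them would require every loss to occur before then, or an endpoint restricted to central-laboratory values, which is not stated.

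Three further inferences also fail. Because "blood and urine samples will be collected at weeks 0, 24, and 48" for the central laboratory, one might think that local values are carried against a central baseline; the article does not say which source feeds the primary outcome. One might think that LOCF favours a claim of similarity; no equivalence or non-inferiority margin is stated and SYKFT and losartan 50 mg are planned as equal. And whether to analyse on a log scale is unrelated to missing data.

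Finally, the per-protocol analysis of completers does not depend on carried final values, and an unseen analysis plan may hold sensitivity analyses, so their absence here is no fault. Completers are a selected group, however, and neither fact changes the method fixed for the principal result.

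**Conclusion.** The point holds as a weakness in the chosen primary method, to be rated as should-fix. With equal 20% loss and half the response reached, LOCF takes 10% off every difference and raises the SD to about 0.28 g, leaving about 56% power for the 0.08 g contrast. This cost depends on f and largely disappears if the response is nearly complete at dropout.

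With unequal loss there is bias as well: about 0.0125 g at the largest gap that the article's reaction rates support, and 0.056 to 0.063 g at an illustrative 10 points, against combination-versus-single differences of 0.05 to 0.10 g. The 10-point figure shows how exposed the design is; it is not an expected value. The gap and the time course are assumptions throughout.

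**What to change.** Before unblinding, replace LOCF in the principal analysis with a likelihood-based mixed model for repeated measures of change in 24-hour proteinuria over the scheduled post-baseline visits. Include treatment, visit, treatment-by-visit, baseline and baseline-by-visit, with an unstructured covariance, and take the week 48 treatment contrasts as the estimates. Keep LOCF as a sensitivity analysis only, and add a delta-adjusted or control-based multiple imputation.

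The visits are already scheduled, so no extra patients or procedures are needed; the cost is revised wording and modest programming. The downside is that the model relies on data being missing at random. The delta-adjusted or control-based analysis is there to show how far the conclusion depends on that.

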### Participants

We propose to enroll 720 participants, mainly from the kidney disease outpatient and inpatient departments. The inclusion criteria are a diagnosis of primary glomerulonephritis, aged 18 to 70 years, blood pressure ≤140/90 mmHg, estimated glomerular filtration rate ≥45 mL/min/1.73 m^2^, 24-hour proteinuria level of 0.5 to 3.0 g, traditional Chinese medicine syndrome conforming to Qi-Yin deficiency, and agreement to participate by the patient or their guardians with written informed consent.

The exclusion criteria are: secondary nephropathy; therapy with glucocorticoids, immunosuppressants, or *Tripterygium* drugs in the last 12 months; therapy with other Chinese patent medicines or decoctions that can reduce proteinuria in the last 2 weeks; therapy with renin-angiotensin system blockers in the last 4 weeks; severe primary disease of the heart, brain, liver, or hematopoietic system, or other serious diseases that can affect the patient’s life; pregnancy or lactation; allergic predisposition or known allergy to the drug composition; blood pressure <90/60 mmHg; unilateral or bilateral renal artery stenosis; mental disorders and poor compliance; suspected or confirmed history of alcohol or drug abuse; and participation in another clinical study at the same period (Table 1).

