#### Outcome measures

The primary efficacy outcome will be the post-treatment change in the 24-hour proteinuria level, and the secondary efficacy outcomes will be the post-treatment changes in the serum creatinine level, estimated glomerular filtration rate, traditional Chinese medicine syndrome score, and serum albumin level. Outcome measurements will be performed at weeks 0, 4, 8, 12, 24, 36, and 48 after enrollment.

In addition to measurement of the primary and secondary efficacy outcomes, the following measurements will be performed at each follow-up visit: routine blood tests (red blood cell count, hemoglobin level, platelet count, white blood cell count, and white blood cell differential) and blood biochemical examination (levels of fasting blood glucose, serum creatinine, blood urea nitrogen, uric acid, alanine aminotransferase, aspartate aminotransferase, total protein, albumin, total cholesterol, triglyceride, low-density lipoprotein, and serum potassium). Furthermore, the levels of C-reactive protein, IgA, IgG, IgM, interleukin-6, and interleukin-8 will be measured at weeks 0, 24, and 48.

Safety indicators will include a reduction in the white blood cell count, liver function abnormalities, hyperkalemia, and other adverse events.

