#### Randomization and allocation

Independent biostatisticians with no relationship to the data management and data statistical analysis team will use the SAS 9.1.3 software (version 9.1.3; SAS Institute, Inc., Cary, NC, USA) to generate random numbers according to the block randomization method. This will allow them to allocate the random numbers into five groups at 1:1:1:1:1 ratio. The investigators will allocate the random numbers to eligible participants according to the enrollment sequence. Each site must recruit at least 10 eligible participants initially, and subsequently recruit participants according to the study pace; random numbers and the matching drugs will be complemented by block size. All trial drugs will be dispensed and reclaimed by an independent drug administrator at each site; this administrator will also be responsible for storing and recording the trial drugs.

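### Baseline adjustment of the primary comparison is left optional and the primary test is left to the observed distribution; a pre-named baseline-adjusted ANCOVA would be at least as precise at almost no cost

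*Protocol article*

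**What the plan says.** All references are to the protocol article.

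- **Endpoint (Outcome measures).** "The primary efficacy outcome will be the post-treatment change in the 24-hour proteinuria level". The week-0 value is collected: "Outcome measurements will be performed at weeks 0, 4, 8, 12, 24, 36, and 48 after enrollment".
- **Entry range (Participants).** Eligible patients have a "24-hour proteinuria level of 0.5 to 3.0 g", a six-fold range.
- **Main method (Statistical analysis).** One rule covers all continuous data: they "will undergo analysis of variance followed by pairwise comparison". No separate model is given for the primary endpoint, so this rule is the one that applies to it.
- **Change of test (same section).** "The Wilcoxon rank sum test or Wilcoxon signed rank test will be used if the data exhibit an abnormal distribution". No criterion for non-normality is given.
- **Adjustment (same section).** "Covariance analysis will be used to assess factors that may affect the efficacy outcomes when appropriate". Neither baseline proteinuria nor site is named, and nothing says what would make adjustment appropriate.
- **Randomisation (Randomization and allocation).** Biostatisticians use SAS "to generate random numbers according to the block randomization method". After each site's initial minimum of 10 participants, "random numbers and the matching drugs will be complemented by block size". Blocks within site are implied but not stated.

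**The concern.** Two things are left open that could be fixed now.

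The first is precision. A patient entering at 0.5 g can fall by at most 0.5 g, and one entering at 3.0 g by up to 3.0 g, so change in grams can depend on the starting value even after that value is subtracted. In an unadjusted comparison of change this dependence stays in the error term. The differences to be detected are small. On the assumed means in the Sample size section, adding SYKFT to losartan 50 mg gains 0.08 g (1.08 − 1.00), and adding it to losartan 100 mg gains 0.05 g (1.10 − 1.05).

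The second is specification. If an unstated look at the distribution decides between ANOVA and a Wilcoxon test, the result may be a difference in means or a rank comparison, and nobody can say in advance which. Likewise, an adjusted analysis chosen after the results are known would be open to challenge, because neither its trigger nor its covariates were set down.

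**Working it through.** **Inputs from the document.** SD of change 0.2 g in every group; 144 per group including a 20% allowance for loss (Sample size); two-sided tests at 0.05 (Statistical analysis). Evaluable per group: 144 × 0.8 = 115.2, taken as 115.

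**The plan's own figure.** At two-sided 0.05 and 90% power, the five-group ANOVA needs 76 per group (95 after loss). Pairwise differences of 0.10, 0.08 and 0.05 g need 85, 132 and 337 (107, 165 and 422 after loss). None of these gives 144. It is reached for 0.10 g if alpha is divided by 4: 115 per group, and 115 / 0.8 = 144. So 144 is not shown to be wrong, but its basis is not stated. It is used below only to fix the 115.

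**Inputs not in the document (assumed).** The baseline-to-follow-up correlation r, from 0.3 to 0.9, and the ratio s of follow-up SD to baseline SD.

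**Direction of the gain.** Set the baseline SD to 1.
- Variance of change = 1 + s² − 2rs.
- Residual variance after ANCOVA on baseline = s²(1 − r²).
- The first minus the second = 1 − 2rs + r²s² = (1 − rs)², which is never negative.

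In large samples, then, ANCOVA is at least as precise whatever r and s are. The two are equal only when rs = 1.

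**Size of the gain.** With s = 1 the ratio of the two variances reduces to (1 + r)/2.

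| s | r = 0.3 | r = 0.5 | r = 0.7 | r = 0.9 |
|---|---|---|---|---|
| 1 | 0.65 | 0.75 | 0.85 | 0.95 |
| 0.7 | 0.417 | 0.465 | 0.490 | 0.405 |
| 0.5 | 0.239 | 0.250 | 0.232 | 0.136 |

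**Power at 115 per group, two-sided 0.05, no multiplicity adjustment, s = 1.** The unadjusted standard error is 0.2 × √(2/115) = 0.0264 g. ANCOVA multiplies it by the square root of the ratio; at r = 0.5 this is 0.0264 × √0.75 = 0.0228 g.
- 0.08 g, unadjusted: 0.08/0.0264 − 1.96 = 1.07, power 85.8%.
- 0.08 g, ANCOVA at r = 0.5: 0.08/0.0228 − 1.96 = 1.54, power 93.9%. Over r = 0.9 to 0.3: 87.5% to 96.4%.
- 0.05 g: 47.4% unadjusted, 59.1% at r = 0.5, and 49.4% to 65.2% over the same range.

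**The change of test.** This was simulated with two arms of 115, 4,000 runs, and a Shapiro-Wilk test at 0.05 deciding between the t-test and the rank sum test. Type I error under the switching rule was 0.052 with normal data and 0.050 with skewed (lognormal-shaped) data. Power for 0.08 g was 0.846 with the rule and 0.846 with the t-test alone under normality, and 0.986 against 0.850 under skew. In these settings the rule cost neither type I error nor power.

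**The case against.** The strongest reply is that an unadjusted comparison of change is valid under randomisation, that covariance analysis is already allowed, and that a covariate list is commonly left to an analysis plan that is not shown. The validity stands: no bias is alleged. The last part stands only in part, because the article does set a main method and does make adjustment discretionary.

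The size of the gain can also be disputed. Assume, for illustration, a baseline SD of 0.6 g, the same follow-up SD, and the planned SD of change of 0.2 g. Then 2 × 0.36 × (1 − r) = 0.04, so r is about 0.94, the ratio is about 0.97, and ANCOVA saves about 3%. This stands: the saving may be small or large, and the document cannot say which.

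Several stronger readings are tempting but not supported:

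- **That the plan ignores baseline.** It does not: change subtracts the week-0 value, and covariance analysis is permitted.
- **That randomisation was stratified by site and the analysis wrongly omits it.** Site blocks are an inference from how numbers and drugs are replenished; stratification is not stated.
- **That the Wilcoxon rule inflates error or loses power.** The simulation shows neither. Its fault is an unfixed test and effect measure.
- **That the signed rank test is meant for comparing arms.** The sentence lists two tests, and the natural reading is rank sum between groups and signed rank within a group.
- **That a log-scale model is required.** Ratios of geometric means would replace the gram-scale change on which the endpoint and the 720 patients are based. That is a debatable trade-off, not a correction.

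**Conclusion.** The point holds as one of efficiency and specification. The only method the article commits to for the primary endpoint is an unadjusted ANOVA of change, adjustment is optional with no covariate named, and the observed distribution may replace the test on no stated criterion.

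The direction of the precision gain does not depend on the assumed values. Its size does: 5% to 35% less variance with equal SDs and r from 0.9 to 0.3, and more if the follow-up SD is smaller than the baseline SD (51% to 86% less for s of 0.7 and 0.5). The power gain of about 8 percentage points for 0.08 g rests on r = 0.5, equal SDs, the planned SD of 0.2 g and 115 evaluable per group. It illustrates the gain and is not an estimate for this trial. Any gain from adjusting for site cannot be sized, since no between-site variance is given.

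**What to change.** Before unblinding:

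1. Name one primary model: ANCOVA of the change in 24-hour proteinuria on treatment and week-0 proteinuria. Using the week-48 value as the response, with the same baseline covariate, gives the same arm differences.
2. State whether blocks were issued within site. If they were, add site to the model, with small sites pooled by a rule set while still blind.
3. Report baseline-adjusted arm differences in grams with 95% confidence intervals.
4. Make the rank-based test a prespecified sensitivity analysis instead of a replacement triggered by the data. A log-scale analysis may be added but is optional.

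The week-0 value is already collected and no extra patients are needed. The Blinding section keeps the statisticians blind to allocation, so the choice can still be made without knowledge of the results. The cost is minor programming, one degree of freedom for baseline, and a few for site. Pooling matters for the last of these, because a site with 10 participants has on average only two per arm.
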